### Research aims

The aim of this research is to determine whether a dialysis-specific OHP (DOHP) will improve the psychosocial health of dialysis patients, compared to usual care. The primary objective is to identify the impact of DOHP on levels of depression and anxiety in those receiving dialysis. Secondary objectives are to evaluate the impact of DOHP on quality of life, self-efficacy, social and workplace functioning, self-management, and illness perceptions of and coping with ESKD.

A full economic evaluation, namely, cost-effectiveness analysis will be performed to provide further evidence on the efficiency of the DOHP by outweighing health gain and impact on the use of health resources associated with DOHP. The perspectives are from the Australian healthcare system and the patient/family. Quality-adjusted life years (QALYs) will be measured using the Assessment of Quality of Life-6D (AQoL-6D) [25] and European Quality of Life-5 dimensions (EQ-5D-3L) [26]. Process evaluation including focus group interviews will also be conducted with patient and staff participants to assess the effectiveness of the DOHP, implementation, and uptake and service delivery.

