### Participants

A minimum of 96 patients initiating dialysis will be recruited into the study. The type of dialysis is haemodialysis, peritoneal dialysis or home dialysis, or collectively known as ‘dialysis’. The following criteria must be met for inclusion in the study: (1) diagnosis of near ESKD confirmed by medical records; (2) expected to commence maintenance dialysis for the first time in the next 3 months or commencement of dialysis in the past 3 months; (3) aged 18 or above; and (4) able to converse in English without an interpreter. Exclusion criteria are: (1) presence of developmental disability or amnestic syndrome impairing their ability to learn from the intervention; (2) participants returning to dialysis following a failed renal transplant; and (3) comorbid serious illness as defined by the treating physician. Individuals who are seeking a mental health professional or taking psychotropic medications will not be excluded from participating.

Power was calculated to detect a medium effect size of *d* = 0.40 using a sample size formula comparing time-averaged differences for continuous outcomes in repeated measurement studies [27]. The power calculations assumed the following: (a) two primary outcome measures (HADS anxiety and depression severity scores); (b) four assessment points (i.e. baseline, 3, 6, and 12 months); (c) a between-repeated measures ρ = 0.70; (d) a study-wide type I error of 0.05 (i.e. a single test α of 0.05 ÷ 5 or 0.01); (f) a type II error rate (β) of 0.20 (power of 0.80); and (g) two-tailed statistical tests. The within-subject correlation (0.70) was based upon a previous OHP trial that demonstrated high correlations over time [22]. The power analysis indicated that 38 participants would be required in each group. Allowing for an attrition rate of 20 %, a total of 96 participants, or 48 in each arm, will be recruited.

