### Statistical analyses

Intention-to-treat analysis will be employed to prevent overestimation of intervention efficacy. Categorical variables will be analysed using chi-squared tests (or Fisher’s exact test for small samples). A mixed-effects model, repeated measures (MMRM) approach will be used to examine the longitudinal profile of the two primary outcome measures at the three time points (3, 6 and 12 months post-baseline). For all MMRM analyses, baseline scores will be used as covariates and the models will include prespecified fixed effects of treatment, clinician and time, in addition to treatment-by-time and treatment-by-clinician interactions. Appropriate adjustments for multiple primary (depression and anxiety) tests will be made, i.e. Bonferroni correction to ensure the risk of type I error is maintained at 5 %. The potential impact of any additional care received by some participants will be assessed in a separate regression analysis using analysis of covariance.

Secondary analyses using analysis of covariance will be conducted to compare change scores during treatment and follow-up points for primary, secondary and process outcomes using the fixed, continuous covariate of baseline score as well as the categorical fixed effects of treatment group, clinician and treatment-by-clinician interactions. Following this, all secondary outcome measures will be assessed, as per above using first a MMRM and then assessing change scores.

Although the attrition rate is not expected to vary by group (intervention vs usual care), we will attempt to identify key predictors of attrition status (i.e. demographic or clinical baseline characteristics) and test for differences between groups. Assuming the data are missing at random, several procedures offer effective approaches that may attenuate attrition. For example, multiple imputation procedures that utilise the expectation-maximization (EM) algorithm with bootstrap estimates of standard errors will be used. A maximum likelihood model with time as a random variable will allow the use of all available data from all assessments, reducing bias and increasing power [40]. Application of these procedures has been shown to provide unbiased estimates, even in the face of substantial missing data [41].

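### Single-step Bonferroni on the two primary HADS scales is valid, but it gives up power that Holm's step-down procedure recovers at the same 5% study-wide error

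*Protocol article*

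**What the plan says.** The Research aims section states: "The primary objective is to identify the impact of DOHP on levels of depression and anxiety in those receiving dialysis". The power paragraph under Participants accordingly lists "two primary outcome measures (HADS anxiety and depression severity scores" and gives one power value, "a type II error rate (β) of 0.20 (power of 0.80", next to a single-test alpha of 0.05 ÷ 5 = 0.01. It gives no power for both scales or for at least one scale, and no correlation between the two HADS scores.

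The Statistical analyses section then fixes the multiplicity rule for the primary tests: "Appropriate adjustments for multiple primary (depression and anxiety) tests will be made, i.e. Bonferroni correction to ensure the risk of type I error is maintained", the study-wide limit being 5%. The wording names the method rather than offering it as an example. Two tests and 5% overall imply 0.025 per scale. No section says that both scales must be significant for the trial to succeed.

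**The concern.** Single-step Bonferroni tests each scale at the divided level whatever the other scale shows. Once one scale has been rejected at 0.025, only one hypothesis remains, and 5% control no longer requires it to be held to 0.025. The written rule holds it there anyway. The trial can therefore report one HADS scale as negative when a procedure with the same study-wide error would report it as positive. With 96 participants that is an avoidable loss.

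A smaller, related point is that the single 0.80 sits beside an objective covering two scales, and the article does not say in words that it is the power for one scale.

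**Working it through.** **1. Error control.** For two tests, Holm compares the smaller p-value with 0.025 and, only if that is significant, the larger with 0.05.
- Both null hypotheses true: a false positive requires the smaller p-value to be below 0.025, exactly as under Bonferroni. The probability is therefore identical: 4.9% at r = 0, 4.5% at r = 0.6 and 4.3% at r = 0.7.
- One null true: it can be rejected only if its own p-value is below 0.05, so the error is at most 5%.

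Neither step uses the correlation between the scales.

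**2. Example with two tests at 5% overall.** Take p = 0.010 and p = 0.035. Bonferroni: 0.010 < 0.025 is positive and 0.035 > 0.025 is negative. Holm: 0.010 < 0.025 is positive, then 0.035 < 0.05 is also positive.

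**3. The plan's own power figure.** The inputs are in the power paragraph.
- Effect size: "Power was calculated to detect a medium effect size of *d* = 0.40".
- Visits counted: "four assessment points (i.e. baseline, 3, 6, and 12 months".
- Method named: "using a sample size formula comparing time-averaged differences for continuous outcomes in repeated measurement studies".
- Correlation over time: "a between-repeated measures ρ = 0.70".
- Two-sided alpha is 0.01 and power is 0.80.

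The usual formula is n per arm = 2(z₁₋α/₂ + z₀.₈₀)² × [1 + (k − 1)ρ]/k ÷ d².
- Variance factor: (1 + 3 × 0.70)/4 = 0.775.
- n = 2 × (2.576 + 0.842)² × 0.775/0.16 = 113.1, so 114 per arm, against the printed 38.
- At 38 per arm the single-test power is 28% at 0.01 and 40% at 0.025.
- A baseline-adjusted mean of three follow-ups has factor (1 + 2 × 0.70)/3 − 0.70² = 0.31. At 0.025 it gives 37 per arm and 81% power at 38, but it is not the printed calculation and does not use the printed alpha.

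The printed 0.80 therefore cannot be taken as established, and the gain from Holm has to be shown under several readings.

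**4. Gain if each scale has 80% power at two-sided 0.025.** The test statistics are bivariate normal with both means 2.241 + 0.842 = 3.083. Their correlation r is an assumption.
- Bonferroni, both scales: P(both p < 0.025).
- Holm, both scales: P(both p < 0.05 and at least one p < 0.025).
- Holm, one given scale: by symmetry, 80% plus half the both-scale gain.

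| r | Both, Bonferroni | Both, Holm | Gain (points) | Per scale, Holm |
|---|---|---|---|---|
| 0 | 64.0% | 75.1% | 11.1 | 85.5% |
| 0.5 | 68.7% | 77.8% | 9.1 | 84.6% |
| 0.6 | 69.9% | 78.6% | 8.7 | 84.3% |
| 0.7 | 71.3% | 79.4% | 8.1 | 84.1% |
| 0.8 | 72.9% | 80.4% | 7.5 | 83.7% |

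The chance of showing at least one scale depends only on the smaller p-value, so the two rules agree: 80% + 80% − 69.9% = about 90% at r = 0.6.

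**5. Gain under other readings, tests at 0.025, r from 0 to 0.8.**

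| Reading | Per scale, Bonferroni | Both, Bonferroni | Both, Holm | Gain (points) |
|---|---|---|---|---|
| 80% at 0.01 as printed, tested at 0.025 | 88% | 77–83% | 86–89% | 6–8 |
| Printed formula, 38 per arm | 40% | 16–30% | 25–39% | about 9 |
| Baseline-adjusted mean of 3 visits, 38 per arm | 81% | 66–75% | 77–82% | 7–11 |

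The levels move widely; the both-scale gain stays at about 6 to 11 points. Per-scale power rises by half of that, about 3 to 6 points.

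**The case against.** The strongest reply is that the Statistical analyses section contains no error: Bonferroni is valid, prespecified and does what the section says. That stands. This is a better choice at little cost, not the repair of an invalid method.

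A reader might go further and infer that the trial has only about 70% power for its stated objective, and that Holm would restore about 79%. The article does not support this, for three reasons.
- No section requires both scales to succeed. Splitting alpha implies that a result on either scale counts, and Holm does not change the chance of at least one. If both were required, no split would be needed: each scale could be tested at 0.05.
- The 70% and 79% need 80% power at 0.025 and r of about 0.6. The article attaches its 0.80 to alpha 0.01 and gives no r. With 80% at 0.01 and tests at 0.025, Bonferroni already shows both scales with probability 81% at r = 0.6.
- The 0.80 does not follow from the printed inputs. Under the printed formula with 38 per arm, the figures at r = 0.6 are about 25% and 35%.

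The numerical example also depends on 0.025. At a per-test level of 0.01, neither 0.010 nor 0.035 falls below the threshold. Across two tests, however, 0.01 each would spend 2%, not the stated 5%.

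Stating power per test is conventional, and the article does label its alpha as single-test. That makes the 0.80 a matter of clarity rather than a misstatement. None of this removes the advantage of Holm, which also raises the power of each scale taken alone.

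**Conclusion.** The point holds as an avoidable loss of power. For the two primary tests at 5% overall, Holm keeps the same study-wide error under any correlation and never rejects less than Bonferroni. With tests at 0.025 and equal true effects on both scales, the both-scale gain is about 6 to 11 points and the per-scale gain about 3 to 6 points, over assumed r of 0 to 0.8 and the readings examined. The ordering of the two rules needs none of these assumptions; the absolute power levels need all of them. The unreconciled alpha (a divisor of 5 against two named tests) and the unreproduced 38 per group are larger, separate problems that Holm does not solve.

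**What to change.** In Statistical analyses, replace the Bonferroni correction with Holm's step-down procedure over the two primary tests: the smaller p-value is tested at 0.025 and, if significant, the other at 0.05. Report 97.5% confidence intervals alongside. Recruitment was ongoing when the article was submitted; the change should be dated and made before outcomes are compared by arm.

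In the power paragraph, say that 0.80 refers to a single scale. Do not insert 70% or 79%. First reconcile the per-test alpha with the two named tests and re-derive the 38 per group; then give any both-scale power with its assumed r and a range.

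The Holm change and the clarification cost one sentence each, with no added participants or data. The small downside is that the 97.5% intervals do not match Holm's decisions exactly: a scale rejected at the second step can have an interval that includes zero.

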## Discussion

CKD and ESKD are both serious and growing health problems that have enormous impact on social and psychological functioning [4–15]. Despite high rates of comorbid depression and anxiety in these patient populations, as well as disquieting evidence of their potential effects on intervention adherence, quality of life, social connectedness and healthcare costs, there has been little development in the area of prevention or management of these conditions [19, 20]. This trial of an 8 + 1 week psychosocial intervention aimed at improving depression and anxiety with further subsequent psychosocial implications will be the first of its kind undertaken in the CKD transitioning to ESKD with dialysis population.

The DOHP has several strengths, primarily the provision of coordinated care aimed at enhancing the psychosocial health of patients experiencing ESKD. We believe that this innovative trial will contribute to the knowledge of interventions aimed at supporting this patient population and will broaden the focus from symptoms to include psychosocial factors such depression, anxiety, self-efficacy, wellbeing and community supports. In addition, we envisage the quality control component of this trial, via process evaluation, will offer further insight into how the intervention can best be adapted and integrated into the general medical setting.

The outcomes associated with this project are significant in terms of enhancing an at-risk population’s quality of life and psychological wellbeing as well as reducing real treatment-related costs and associated pressures on the renal healthcare system. Furthermore, the proposed RCT will aim to address and reflect the key intent of this major research initiative; a multifactorial, long-term collaborative approach developed via end-user-driven research partnerships that will deliver health benefits to enable Australians with ESKD to age well and productively.

### Trial status

Patient recruitment was ongoing at the time of manuscript submission. Data collection will continue until at least December 2017.

ANZCTR no. 12615000810516.

## Abbreviations

AQoL-6D: Assessment of Quality of Life-6 dimensions
Brief-IPQ: Brief Illness Perception Questionnaire
Brief COPE: abbreviated version of the COPE Inventory
CEQ: Credibility/Expectancy Questionnaire
CKD: chronic kidney disease
CTF: collaborative therapy framework
DOHP: Dialysis Optimal Health Program
EM: expectation-maximization
EQ-5D-3L: European Quality of Life-5 dimensions-3 levels
ESKD: end-stage kidney disease
GSE: General Self-efficacy Scale
HADS: Hospital Anxiety and Depression Scale
HCUQ: Health Care Utilisation Questionnaire
KDQoL: Kidney Disease Quality of Life
MINI: Mini-International Neuropsychiatric Interview
MMRM: mixed-effects model, repeated measures
OHP: Optimal Health Program
QALY: quality-adjusted life year
RCT: randomised controlled trial
TEI-SF: Treatment Evaluation Inventory-Short Form
TIPI: Ten-Item Personality Inventory
TRIPOD: Translating Research, Integrated Public Health Outcomes and Delivery
WSAS: Work and Social Adjustment Scale
